## Abstract

•First North American RCT to evaluate crowdsourced response for out-of-hospital cardiac arrest (OHCA).•PulsePoint Respond mobile app alerts aim to boost CPR and AED use before paramedics arrive.•Employs automated real-time randomization process integrated within 9-1-1 dispatch systems.•Registry-linked outcomes assess PulsePoint Respond across diverse settings.•Trial results to guide policy on app-based community responder approaches for OHCA.

First North American RCT to evaluate crowdsourced response for out-of-hospital cardiac arrest (OHCA).

PulsePoint Respond mobile app alerts aim to boost CPR and AED use before paramedics arrive.

Employs automated real-time randomization process integrated within 9-1-1 dispatch systems.

Registry-linked outcomes assess PulsePoint Respond across diverse settings.

Trial results to guide policy on app-based community responder approaches for OHCA.

## Introduction

Out-of-hospital cardiac arrest (OHCA) is a time-critical emergency affecting approximately 60,000 Canadians and 356,000 Americans annually. Fewer than 10 % survive to hospital discharge.^1^, ^2^ Early cardiopulmonary resuscitation (CPR) and automated external defibrillator (AED) use can increase the odds of survival by two to three times,^3^, ^4^, ^5^, ^6^ but only if these interventions occur rapidly. The median paramedic response time is approximately seven minutes in optimized urban systems and can exceed 14 min in rural areas or hard-to-access urban locations.^7^, ^8^ To mitigate delays in professional response, efforts have been made to encourage bystander CPR and AED use while professionals are en route. Despite sustained global efforts to promote CPR and public access defibrillation, bystander CPR occurs in fewer than 50 % of OHCA cases, and bystander AED use remains below 3 % in many communities.^2^

Community volunteer responder programs using mobile apps, text messages, or other dispatch technologies have emerged as promising strategies to reduce delay to CPR and defibrillation. However, the International Liaison Committee on Resuscitation (ILCOR) has classified the evidence supporting community first responders engaged by technology as “very low-certainty” and has called for clinical trials to generate more robust evidence.^9^ The only published randomized controlled trial (RCT) to date was done in Scandinavia,^10^ highlighting the need for replication in other geographical contexts.

To address the evidence gap, we have designed and implemented a RCT to evaluate the impact of a commonly used mobile device application called “PulsePoint Respond” designed to crowdsource bystander resuscitation for patients who experience OHCA. Our primary objective is to determine whether “CPR Needed” alerts sent via the PulsePoint Respond app during dispatch procedures increase the occurrence of bystander CPR or AED use before professional responders arrive, compared with standard dispatch procedures without PulsePoint alerts. Our secondary objective is to examine how cardiac arrest event characteristics (e.g., initial rhythm, location type, time of day) and system characteristics (e.g., PulsePoint user density) influence the likelihood of bystander resuscitation following a PulsePoint alert.

## Methods

We used the SPIRIT 2025 checklist of items to address in a randomized controlled trial protocol to structure this report (Supplementary Material 1).^11^

### Open science features

The trial website can be found at https://emergencymed.queensu.ca/research/publications-research-studies. This report is based on protocol version 4.0, modified on October 28,2024. The full trial protocol and analysis plan is available from the corresponding author on request. With appropriate research ethics approval, agreement from participating emergency medical services (data owners), and data-sharing agreements de-identified participant data (including data dictionary) and statistical code will be made available on request to the corresponding author.

### Design

This is a pragmatic, parallel-group, superiority randomized controlled trial.

### Setting

This study is being conducted in two locations: British Columbia Emergency Health Services (BCEHS), which serves the Canadian province’s 5.7 million residents across urban, suburban, and rural settings, and the Columbus Division of Fire, which serves a mostly urban population of 900,000 in the U.S. city of Columbus, Ohio.

### Financial support, study registration and ethics review

This project is supported by an operating grant from the Canadian Institutes of Health Research (Partnerships for Health System Improvement program, FRN #148168), and an investigator-initiated grant from ZOLL Medical Corporation. We registered the trial at clinicaltrials.gov on March 16, 2021 (ClinicalTrials.gov ID NCT04806958, https://www.clinicaltrials.gov/study/NCT04806958#study-plan). The protocol was approved by the Queen’s University Health Sciences & Affiliated Teaching Hospitals Research Ethics Board (REB) (TRAQ # 6020246), the University of British Columbia REB (H17-00310), and the Ohio State University Institutional Review Board (IRB)(#2017H0440) with a waiver of the requirement for informed consent.

### Pre-trial community consultation

Formal community consultations were mandated by the Ohio State University IRB to assess community attitudes toward the study design, the waiver of consent, and the overall acceptability of the intervention. In February 2019 we deployed an online survey targeting residents of Columbus and a telephone survey for residents in both British Columbia and Columbus. The online survey garnered 187 responses indicated support for the proposed clinical trial: 97 % of respondents viewed the study as “very important” or “important,” and 95 % reported feeling “very comfortable” to “neutral” with the planned research. Less than 4 % expressed concerns about the waiver of consent. The telephone survey was conducted by a contract survey organization (HR2 Analytics, Bellevue, Washington). In Columbus (*n* = 70), 99 % of respondents reported being “very comfortable”, “comfortable” or “neutral” with the proposed study, and 93 % expressed strong support for its importance. Similarly, in BC (*n* = 30), 97 % were comfortable with the study, and 90 % viewed the research as important. Only 7 % cited privacy concerns, including potential unauthorized sharing of personal health information or real-time location.

### Comparison groups defined and characterization of the control group

The treatment group receives activation of the PulsePoint Respond system in addition to standard emergency medical dispatch procedures. The control group receives standard emergency dispatch procedures only. Both study locations follow established dispatch protocols. BCEHS has three linked provincial communications centers that use Medical Priority Dispatch System (MPDS) protocols to categorize emergencies, trigger telecommunicator CPR instructions, and dispatch ambulances and partnered first‑responder fire units to high‑priority calls such as suspected cardiac arrests. In Columbus, the Division of Fire operates a fire‑medic model with Basic Life Support and Advanced Life Support teams dispatched simultaneously for cardiac arrests, responding from 35 stations equipped with fire apparatus and medic units. Both systems ensure rapid professional response; our trial evaluates whether adding PulsePoint‑activated community responders provides incremental benefit. The study intervention concludes in the prehospital setting. All care provided to participants allocated to either group is at the discretion of the clinicians in the prehospital and hospital settings.

### Characterization of the treatment group: PulsePoint respond

PulsePoint Respond consists of two main components: the PulsePoint interface software and the PulsePoint Respond mobile device application. The interface software is installed on computer-assisted dispatch (CAD) systems used by emergency call-takers to manage emergencies and coordinate paramedic dispatch. The mobile device app is downloaded by community volunteers onto their own mobile phones. During a 9-1-1 call, the PulsePoint interface software screens incident data in real time. If the call is coded on the local CAD as a suspected cardiac arrest in a public location, the PulsePoint system is activated. It then sends “CPR Needed” notifications to nearby users of the PulsePoint Respond app who have opted in to receive these type of alerts and are within approximately 400 m of the incident. Unless users opt out, the notification overrides “Do Not Disturb” settings and plays an audible alarm even when the device is muted. Once acknowledged, it opens an interactive map showing the incident location and nearby public access AEDs (Fig. 1). The PulsePoint notification process operates automatically and does not require the 9-1-1 call-taker to activate the system. To facilitate community uptake, both study sites launched communication strategies, including websites, press releases, media interviews, and social media campaigns aiming to maximize PulsePoint Respond app downloads. We engaged healthcare and resuscitation organizations including CPR training groups, responder unions, public defibrillation charities, and life-saving equipment companies, to promote app downloads amongst members.

**Fig. 1 f0005:**
[figure not shown]
A PulsePoint “CPR Needed” alert with an interactive map showing the location of the user (blue dot) in relation to the location of the emergency (red heart icon) and nearby public access defibrillators (yellow AED icon) (For interpretation of the references to colour in this figure legend, the reader is referred to the web version of this article).

### Automated patient recruitment and randomization

Inclusion criteria for the study are 1) 9-1-1 calls assigned as “suspected” or “confirmed” OHCA, and 2) OHCA confirmed as paramedic-treated, public location OHCA. Exclusion criteria include 1) a traumatic cause of cardiac arrest, 2) cardiac arrest occurring in the context of a dangerous scene as determined by the 9-1-1 call-taker, 3) paramedic-witnessed cardiac arrest, 4) cardiac arrest not treated by paramedics (Do Not Resuscitate or signs of obvious death), 5) cardiac arrest occurring in nursing homes. To operationalize these criteria and facilitate the recruitment of OHCA patients at the time of the 9-1-1 call, we undertake the following processes. All 9-1-1 calls coded as possible OHCA incidents occurring in non-residential locations in the computer-assisted dispatch systems of participating communities are automatically enrolled into the trial and undergo random allocation to a treatment group by the PulsePoint server. In BC, Medical Priority Dispatch System codes 09D01 (ineffective breathing), 09E01 (respiratory arrest), 09E02 (uncertain breathing status), 11D01 (choking with altered level of consciousness), 11D02 (choking with abnormal breathing), 11E01 (verified choking), 12D01 (convulsions with absent breathing), and 14D01 (unconscious drowning) define possible OHCA. In Columbus, Association of Public-Safety Communications Officials (APCO) call designators “Cardiac Arrest”, and “Drowning” are used. When the trial was launched, Columbus had also included “Unconscious Overdose”, and “Unconscious Person”, but these codes were later removed from our randomization trigger criteria due to very low specificity for OHCA. Random allocation occurs using code embedded within the PulsePoint server activation process for “CPR Needed” alerts. The code references a randomization table generated by the study statistician enabling 1:1 random allocation, stratified by site, using permuted blocks of varying sizes. For each eligible 9-1-1 call, the next entry in the randomization table determines group assignment. If allocated to the treatment group, the PulsePoint activation proceeds as designed. If assigned to the control group, the process stops before any “CPR Needed” notifications are sent. Each allocation is automatically logged by the server and used by study staff to track enrollment.

### Primary analysis eligibility and case confirmation

Randomized patients will be considered eligible for the primary analysis only if they satisfy inclusion criteria, meet no exclusion criteria, and also have at least one PulsePoint responder within 400 m at the time of the 9-1-1 call. Because the intervention and its intended effect must occur before paramedic arrival, randomization must also occur before patient eligibility for the primary analysis can be determined. Study staff retrospectively review each randomized case to determine whether it meets criteria for inclusion in the primary analysis. This approach allows rapid randomization but will introduce many post-randomization exclusions (Fig. 2).

**Fig. 2 f0010:**
[figure not shown]
CONSORT diagram showing the enrollment, randomization, and application of inclusion and exclusion criteria to define the primary analysis cohort in the PulsePoint randomized controlled trial.

We use pre-existing out-of-hospital cardiac arrest registries to determine eligibility and to capture patient, event, response, and outcome data. Cases from British Columbia are linked to the BC Cardiac Arrest Registry,^12^ and those from Columbus are matched to the CARES registry.^13^ Matching is based on a unique agency incident number, date, time, and location. If no match is found within six months of the incident date, the case is coded as non-OHCA and is excluded. Both registries define cardiac arrest as cases involving CPR or defibrillation by paramedics, or a shock delivered by a bystander AED before their arrival and use validated methods to ensure complete case capture within their regions.

An important determinant of primary analysis eligibility is whether paramedics-initiated resuscitation. Only paramedic-treated cardiac arrests are included, so local protocols guiding initiation of treatment may influence post-randomization exclusions and introduce selection bias. In British Columbia, paramedics initiate CPR unless a valid “No CPR” directive or signs of obvious death (e.g., decapitation, decomposition, rigor mortis) are present. Termination requires online medical control and completion of a structured assessment verified by two providers. In Columbus resuscitation is withheld under a “Dead on Arrival” protocol for patients with irreversible signs of death including decomposition, rigor mortis, dependent lividity, or extreme mottling. Termination may occur after 20 min of advanced life support without ROSC in non-shockable rhythms and requires online medical control consultation and detailed documentation.

### Blinding

The entire randomization and allocation process occurs with blinding of 9-1-1 callers, 9-1-1 call-takers, responding paramedics and firefighters, bystanders, patients, investigators, and the study statistician. Each randomization event is automatically logged by the system and labeled only as “Group A” or “Group B” to preserve allocation concealment. A key, linking group labels to intervention status, is maintained by an independent statistician who will only unblind the study groups after analysis is complete.

### Outcome measures

Outcome selection and reporting are consistent with the Utstein Cardiac Arrest Registry Template.^14^ The primary outcome is bystander resuscitation attempt, defined as the occurrence of either bystander CPR or bystander AED use prior to the arrival of professional emergency responders. Secondary outcomes include bystander CPR, bystander AED use (attachment of pads to the chest), bystander AED shock delivery, return of spontaneous circulation, survival to hospital discharge, and survival to hospital discharge with good functional outcome (Cerebral Performance Score 1 or 2). We planned to collect and report modified Rankin Score, but later discovered that this measure is not available in the cardiac arrest registries. Secondary safety outcomes include paramedic response time interval, on-scene time interval, and the proportion of patients receiving bystander interference with the resuscitation effort (determined from emergency medical service crew safety reports and primary documentation in the clinical record). Secondary system performance outcomes include the number of PulsePoint application downloads for each agency over the course of the trial, the number of PulsePoint application users notified for each call, the sensitivity of PulsePoint activation calculated as the proportion of OHCA during the trial resulting in a study allocation event, and the false positive rate for PulsePoint activation calculated as the proportion of PulsePoint activations associated with non-cardiac arrest incidents.

### Sample size considerations

We calculated our target sample size to detect a 15 % absolute increase in bystander resuscitation attempts between treatment groups. The study steering committee determined this to be the minimal clinically important difference through consensus. Using updated simulations assuming a consistent odds ratio across strata with varying baseline event rates, we initially targeted a total sample size of 522 patients to achieve 90 % power, assuming a two-sided alpha of 0.05. However, partway through the trial, we revised the target sample size due to slower-than-anticipated recruitment, limited funding, and concerns about the feasibility of an extended study duration. To address these constraints, we reduced the target power to 80 %, yielding a revised sample size of 340 patients (170 per group). We did not account for missing patients in our revised calculations because recruitment data at the time indicated <1 % loss to follow-up.

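### Lowering power from 90% to 80% takes 522 patients to about 390, not 340; the paragraph must say what else changed, because the power of 340 depends on it

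*Protocol article*

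**What the plan says.** All the figures are in the protocol article, Methods, Sample size considerations. The trial is sized "to detect a 15 % absolute increase in bystander resuscitation attempts between treatment groups". The method is described as "Using updated simulations assuming a consistent odds ratio across strata with varying baseline event rates", and on that basis "we initially targeted a total sample size of 522 patients to achieve" 90% power, "assuming a two-sided alpha of 0.05".

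The paragraph then explains that recruitment, funding and feasibility forced a smaller target. It says that the power was lowered to 80%, "yielding a revised sample size of 340 patients (170 per group". The lower power is the only change named as producing the new number.

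The next sentence adds: "We did not account for missing patients in our revised calculations", because loss to follow-up was below 1% at the time. The paragraph does not say whether the 522 contained an allowance for missing patients, and it gives no baseline event rates. Elsewhere in Methods, allocation is 1:1 stratified by site, and the primary test is a site-stratified Mantel-Haenszel chi-square.

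**The concern.** The article prints two pairs of sample size and power and links them by one stated change. The effect of that change on sample size can be worked out almost without knowing the event rates, and it does not lead from the first pair to the second. The text therefore either leaves out a second change or gives a power figure that does not belong to 340.

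This matters because 80% is the figure against which a null or inconclusive result will be read. The target was cut during the trial for practical reasons. By 12 May 2025, 288 of the 340 patients were in the primary analysis dataset. A reader who scales from the 522 will conclude that the trial has about 74% power. A reader who trusts the 340 will conclude that it has about 80%. The paragraph allows both readings.

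**Working it through.** **Inputs from the article.** Initial N = 522 at 90% power; revised N = 340 at 80% power; two-sided alpha 0.05; 15-point absolute difference; 1:1 allocation. Baseline rates are not given, so every rate below is an assumption.

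**1. What the power change does alone.** With everything else fixed, N is proportional to (z for alpha/2 + z for power)².

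- Ratio N(90%)/N(80%) = ((1.960 + 1.2816)/(1.960 + 0.8416))² = 1.339.
- Printed ratio: 522/340 = 1.535.
- 522/1.339 = 390, which is 50 more than 340.
- Conversely, 340 × 1.339 = 455 would be the 90% size that matches 340 at 80%.

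The ratio hardly depends on the method. Expressed as N(80%)/N(90%), it is about 0.75 with the pooled two-proportion formula and with a stratified common-odds-ratio approximation, 0.76 to 0.77 with continuity correction, and 0.72 to 0.75 one-sided. The printed pair gives 340/522 = 0.651.

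**2. Power of 340 if 522 is truly the 90% size.** Φ(3.2415 × √(340/522) − 1.960) = Φ(0.656) = 0.744, or about 74%.

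**3. Does 340 reproduce on its own?** The pooled two-proportion formula for a 15-point difference at 80% power gives:

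| Assumed control rate | Total N, 80% power | Total N, 90% power | Power with 340 |
|---|---|---|---|
| 30% | 326 | 434 | 81.8% |
| 35% | 340 | 454 | 80.2% |
| 42.5% | 348 | 464 | 79.2% |
| 50% | 340 | 454 | 80.2% |
| 55% | 326 | 434 | 81.8% |

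So 340 is exactly the 80% size at 35% versus 50% or 50% versus 65%. The power of 340 is lowest, at 79.2%, at a control rate of 42.5%.

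**4. Does 522 reproduce with the same formula?** Not without inflation. The largest 90% size is 464, or 490 with continuity correction. With inflation it does: 454 × 1.15 = 522.1, and 454/(1 − 0.13) = 521.8. An allowance of 13 to 15%, depending on how it is applied, therefore reconciles the two numbers with effect, rates, alpha and test unchanged.

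**5. Could 522 be uninflated under the method the article names?** Yes. Suppose the 15 points apply at the average baseline, and the resulting common odds ratio is applied to two equal strata with different baselines.

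- Average 35%: odds ratio = (0.50/0.50)/(0.35/0.65) = 1.857.
- Strata at 20% and 50% then rise to 31.7% and 65.0%. The mean difference is (11.7 + 15.0)/2 = 13.4 points, not 15.
- Total N at 90% = 2 × [(1.960 × √V0 + 1.2816 × √V1)/d]², where d is the mean difference, V0 the mean over strata of 2p̄(1 − p̄), and V1 the mean of p₀(1 − p₀) + p₁(1 − p₁). With V0 = 0.436, V1 = 0.427 and d = 0.1335, N is about 510.
- The same steps around 40% (strata at 25% and 55%) give about 513. With strata 20 points either side of 35% or 40%, N is about 566 or 562.

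An uninflated 522 at 90% is thus attainable with a plausible spread of baselines. The ratio between the two powers stays at 0.748 in these cases, so 340 would still fall short of 80%.

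**The case against.** The strongest defence is that the sentence after the 340 already signals a second change. To say that the revised calculation made no allowance for missing patients, and to justify this by recruitment data, most naturally implies that the earlier calculation did make one. Read together, the two sentences describe lower power and no allowance, and step 4 shows that this can give exactly 522 and 340. The current target also stands on its own under the plain formula, with 79.2% power in the worst case. And an article that condenses a fuller protocol may leave out baseline rates and the inflation factor of a superseded target.

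Much of this stands. A reader might infer that the two pairs cannot rest on common assumptions. That is too strong, because they can share effect, rates, alpha and test if only the 522 was inflated. A reader might also infer that the trial's real power is 74%. The article does not establish that either; it follows only if the 522 was uninflated and nothing but power changed.

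Two things do not stand. The allowance is inferred: the article presents 522 as the number needed for 90% power and nowhere says that it was inflated. Nor does the ceiling of 464 prove an allowance. It belongs to the plain two-proportion formula, whereas the article names a stratified common-odds-ratio simulation, which can reach 522 without one. The complaint also goes beyond omitted detail, because two printed figures and the stated link between them do not agree.

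**Conclusion.** The concern holds in a limited form. The statement that lowering power to 80% gives 340 is wrong as written: that change alone gives about 390. Something besides power also changed, or the power stated for 340 is wrong. This conclusion needs no assumption about event rates.

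The power of 340 depends on a fact the article does not supply. It is about 80% if the 522 held a missing-data allowance of about 13 to 15% and the rates were near the assumed 35% versus 50% or 50% versus 65%. It is about 74% if 522 was an uninflated 90% size and the other assumptions were kept. A third possibility is that the rates or the calculation method changed between the two targets; the power of 340 then depends on the new inputs. The article does not allow a choice among these. It therefore does not show that the target of 340 is inadequate, only that its stated derivation does not support the stated power.

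**What to change.** Correct the sample size paragraph so that it:

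- says what changed besides the target power when 522 became 340;
- gives the missing-data allowance contained in the 522, or says that there was none;
- gives the baseline rate in each stratum and the common odds ratio actually used; and
- reports the power of 340 from that same stratified simulation.

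If the 522 held no allowance and no other assumption changed, the power at 340 should be restated as about 74%. The figures of 454 evaluable patients, a 15% allowance and a 35% or 50% control rate are back-calculated here to show that a reconciliation exists. They should not be written into the protocol unless the sponsor confirms them.

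The cost is one rewritten paragraph and, at most, a rerun of a simulation that already exists. No extra patients are needed. The correction is best made before the results are reported, so that the power statement cannot appear to have been chosen to fit them.
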